### Follow-up cohorts

The recruitment of follow-up participants will take place under three different categories: a) household based follow-up; b) telephonic follow-up; and c) passive or need-based follow-up, serving as control group. The clients recruited under category ‘a’ will receive a scheduled follow-up from FHE at 1, 3, 6, 9, and 12 month. Similarly, the clients recruited under category ‘b’ will receive a telephone call from FHE at the scheduled frequency similar to category ‘a’. In addition, the participants of both the categories (‘a’ & ‘b’) can also seek medical advice from FHE based on need (unscheduled contact). While, category ‘c’ participants will not receive any scheduled intervention from FHE but can only seek FHE’s assistance in case of any medical need.

### Sample size

In order to detect 6% difference amongst the categories, with an 80% power and using sampling software PASS 11, it was estimated to have 414 clients in each of the three groups. Around 1366 clients will be recruited to account for 10% attrition rate. Based on services statistics the estimated sample can be achieved if all the clients at each clinic (who gives informed consent) are registered during the (specified) period for 3-4 months. Thereby clinics having high clientele will contribute more to the sample (to hold proportionality assumption).

### Sampling strategy

Based on preliminary data taken from the field, it is estimated that around 40% of the LARC users have mobile phones [31] thus due to shorter recruitment time, selection of follow-up participants will be done following consecutive sampling. The reason for selecting consecutive sampling over randomization was mainly the long recruitment periods and the budgetary implications. After screening, all the clients receiving LARC during 3-4 months (Nov 2013 till Feb 2014) period will be briefed about follow-up and invited to participate in the follow-up based on their informed consent. Clients will be asked to voluntarily choose the group (among the three described above) under which she would like to be enrolled. Once the desired sample of any specific group is achieved, that group will be eliminated as an option for subsequent clients to opt for. A format will be given to each service provider to keep a track of client enrollment under each group. The same information shall be recorded on the baseline and follow-up form so as to ascertain the selection is performed as per the protocol.

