**FP method taken**			
IUD	78.5	85.3	85.0
Implant	21.5	14.7	15.0
***P-value***	***0.01****		

*Groups: Telephone group will receive a telephone call at the scheduled frequency; Physical group will receive household based follow-up, and Passive group category participants will not receive any scheduled intervention but can only seek assistance in case of any medical need.

^1^
http://www.forex.pk/open_market_rates.asp.

Majority of the women in all three categories had no formal education (observed as 36.3%, 40.8% and 43.2% for Telephone, Physical and Passive categories respectively).

Moreover the ‘type of client’ indicator showed that majority i.e. Telephone (95%), Physical (90.2%) and Passive (91.6%) obtained their FP services via vouchers. The percentage for IUCD uptake was 78.5%, 85.3% and 85% for Telephone, Physical and Passive categories respectively.

The majority of all three categories showed a favorable view of the husband with regards to using a contraceptive method (refer to Table 2).

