**Husband’s view on couple using a contraceptive method**			
Favors	81.7	71.8	74.3
Dislikes	8.3	15.9	13.9
Don’t know/unsure	10.0	12.3	11.8
***P-value***	***<0.01***		

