## Limitations

The follow-up will assess early discontinuation up to 12 months. There may be likely chance of some recall bias in exact date/timing of discontinuation as the data will be collected immediately after the last (12-month) follow-up visit. Providers’ bias is also expected for specific FP methods, furthermore due to non-randomization, clients’ observed and unobserved characteristics may confound the results.

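### Clients choose their own follow-up group, so a crude telephone-household comparison would be confounded, and the part that can be sized favours declaring telephone non-inferior

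*Protocol article*

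**What the plan says.** The Design section calls the study a multi-centre, prospective non-inferiority trial. The hypotheses at the end of Background and context state that telephone follow-up is not inferior to household follow-up on LARC continuation. The indicators listed there include cumulative discontinuation to 12 months by study arm.

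Under Sampling strategy, allocation is by client preference: "Clients will be asked to voluntarily choose the group (among the three described above) under which she would like to be enrolled". Two things limit that choice. The same section estimates that "around 40% of the LARC users have mobile phones". It also sets a quota rule: "Once the desired sample of any specific group is achieved, that group will be eliminated as an option for subsequent clients to opt for".

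The Sample size section gives 80% power and 414 clients per group. Its only statement of effect size is "In order to detect 6% difference amongst the categories". It names neither a non-inferiority margin nor an alpha.

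Baseline results are reported for 424 telephone, 409 household (labelled Physical) and 428 passive clients. On method, the text under Table 1 reads: "The percentage for IUCD uptake was 78.5%, 85.3% and 85% for Telephone, Physical and Passive categories respectively". Table 2 reports, among other items, "Husband’s view on couple using a contraceptive method". Limitations says that, without randomisation, "clients’ observed and unobserved characteristics may confound the results".

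**The concern.** When women pick their group, the groups can differ in their chance of continuing LARC before any follow-up takes place. In a non-inferiority comparison the direction of that difference matters. If the women who choose telephone would have continued more often anyway, telephone follow-up could be worse than household follow-up and still pass. Such a bias is anti-conservative, and a general caveat does not deal with it.

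This contrast carries the study's only effectiveness hypothesis. The article treats household follow-up as the gold standard, and its Discussion hopes that the findings will guide a large cadre of outreach workers. A false finding of non-inferiority would support replacing household visits with calls.

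**Working it through.** **1. The article's sample size.** Alpha, margin and base rate are not stated, so 414 can be neither confirmed nor refuted. One set of inputs gives it exactly: a 6-point margin, 14% discontinuation in both arms, one-sided alpha 0.05 and 80% power.

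n = (1.645 + 0.842)² × 2 × 0.14 × 0.86 / 0.06² = 413.6, rounded up to 414.

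The total also follows: 3 × 414 × 1.1 = 1366.2. I therefore take 6 points as the margin below, as an assumption, and show both 0.05 and 0.025 one-sided.

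**2. Baseline imbalance, telephone vs household.** Percentages are from Tables 1, 2, 3 and 5. The p-values are Pearson chi-square on counts rebuilt from those percentages.

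| Item | Telephone | Household | p | Plausible direction |
|---|---|---|---|---|
| IUD (rest implant) | 78.5% | 85.3% | 0.011 | favours telephone |
| Husband favours contraception | 81.7% | 71.8% | 0.001 (three categories) | favours telephone |
| Husband knows of insertion | 83.3% | 76.3% | 0.012 | favours telephone |
| Woman's education secondary or higher | 35.8% | 24.5% | 0.0003 | favours telephone |
| No method discussed in counselling | 6.1% | 11.0% | 0.012 | favours telephone |
| Age 35 or over | 22.9% | 28.9% | 0.049 | may favour household |
| 0-2 living children | 38.0% | 32.0% | 0.07 | may favour household |
| Voucher client | 95.0% | 90.2% | 0.008 | unclear |

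Secondary or higher sums three rows of Table 1: 25.7 + 6.1 + 4.0 and 17.4 + 4.9 + 2.2. Except for method, the directions are judgements; the article gives no prognostic effects for these items.

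**3. The part that can be sized.** Background and context gives 12-month discontinuation of 16.3% or 26% for IUD and 10% for implant. With no effect of follow-up at all:

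- IUD 16.3%: telephone 0.785 × 16.3 + 0.215 × 10 = 14.95%; household 0.853 × 16.3 + 0.147 × 10 = 15.37%; bias 0.43 points.
- IUD 26%: telephone 22.56%; household 23.65%; bias 1.09 points.

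**4. Effect on the false non-inferiority rate.** Suppose telephone is truly 6 points worse, with 414 per arm. The crude difference is then centred on 6 minus the bias b, and the rate is Φ(b/SE − z). SE comes from the household rate p and the telephone rate p + 0.06 − b.

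| Household rate | Bias (points) | SE | From 5% | From 2.5% |
|---|---|---|---|---|
| 15.4% | 0.43 | 0.0267 | 6.9% | 3.6% |
| 23.6% | 1.09 | 0.0305 | 9.9% | 5.5% |
| 15.4% | 1.09 | 0.0266 | 10.9% | 6.1% |

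The first two rows pair each bias with its own base rate. The third sets the larger bias against the smaller SE and is an outer bound.

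**5. Phone overlap.** The three groups total 1,261. If 40% own a phone (504) and all 424 telephone clients do, 80 owners remain among the other 837, or about 10%; that is about 39 of the 409 household clients. At 50% or 60% ownership the share among the others is 25% or 40%.

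A comparison of 39 household owners with 424 telephone clients, at 14% discontinuation and a 6-point margin, has SE √(0.14 × 0.86 × (1/39 + 1/424)) = 0.058. Power at one-sided 0.05 is Φ(0.06/0.058 − 1.645), about 27%.

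**The case against.** The strongest reply is that the article describes no unadjusted analysis. It names no estimator, and a full protocol or analysis plan may set out adjustment; tabulating these covariates by group is compatible with that. The weakness is also declared under Limitations, and Sampling strategy explains why randomisation was not used. All of this is right. A reader might infer from the indicators by arm that a crude comparison is planned, but the documents do not say so, and the point holds only conditionally. The declared limitation still gives neither direction nor remedy.

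A reader might also add assumed effects of husband's support or education and reach a total bias of 2 points or more. The documents do not support such a figure. An assumed 10-point risk difference for husband's approval would add 0.099 × 10 = 1.0 point, but the same assumption for age or family size would take off 0.06 × 10 = 0.6. Even the method-mix figure compares IUD and implant rates from different cited sources.

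A third tempting reading is that the contrast is simply phone owners against non-owners. That depends on applying a preliminary estimate for LARC users to the enrolled women, and it weakens quickly at 50-60% ownership. Nor does absence from the published tables show that phone access went unrecorded, since the questionnaire is not shown. Whether the quota rule ever closed a group is also unclear: 424 and 428 exceed 414, but all groups are below 1366/3, about 455.

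**Conclusion.** The concern holds in conditional form. Self-selected, phone-limited groups are fixed by the article, and its tables show that telephone and household clients differ on several plausible predictors of continuation. A crude comparison by arm would therefore be biased.

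Only the method-mix part can be sized from the documents: 0.4 to 1.1 points in favour of telephone. With 6 points assumed as the margin, that moves false non-inferiority from 5% to about 7-10% on matched rates (11% at the outer bound), or from 2.5% to about 3.5-6%. The net direction of all confounders is probably towards telephone, but that is a judgement.

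Severity is should-fix: enrolment is complete and allocation cannot change, but the analysis and the wording of the conclusion can.

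**What to change.** 1. Base the non-inferiority conclusion on an adjusted 12-month risk difference, by standardisation or propensity weighting, and require its confidence limit to clear a stated margin. Adjust for method, husband's view and knowledge, woman's and husband's education, voucher status, age, parity, counselling received, facility and enrolment date. Report the crude difference as secondary.
2. If phone access at enrolment is not already on record for household and passive clients, ask about it at the next contact or the 12-month interview. Word the question to refer to enrolment, because current access would be a post-baseline measure. Report the overlap by group.
3. State in advance that adjusting for other covariates cannot repair near-separation on phone access. A comparison among phone owners only would be a low-powered sensitivity analysis. If overlap is thin, limit the conclusion to an association among phone users.

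The cost is some analysis work, at most one extra question, wider intervals (possibly much wider if overlap is poor) and a more guarded conclusion.

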### Tool

A structured questionnaire at baseline and 12-month will be administered to document socio-demographic characteristics and user-related reasons (decision making, acceptability, costs, convenience of method type, timing) and health-related reasons reported by the women. The questionnaire was developed by MSS and reviewed by Department of Reproductive Health and Research, WHO. Moreover, all the enumerators will be given thorough training on all the questionnaires.

### Implementation

Once the client adopted the LARC, she will be asked to participate in the follow-up. As described above, the women enrolled under the active categories (‘a’ & ‘b’) will receive counseling on side-effect management, through an adapted manual used in the Family Advancement for Life and Health (FALAH) project [32] at 1, 3, 6, 9 and 12-month post IUCD insertion. The FALAH was a family planning project supported by the United States Agency for International Development (USAID) whose aim was to protect the health and well being of mothers, newborns and children through the adoption of birth spacing by eligible couples in Pakistan [33]. The same manual will be used to assist women with side-effect management as per need. In order to minimize dropouts/lost-to-follow-up, all the clients will be informed about the detailed follow-up procedures, while taking informed consent. For schedule visits, the FHEs will be reimbursed for their transportation cost. Similarly, FHEs will also be paid for telephone call expenses.

## Baseline information

### Socio-demographic characteristics and participants’ profile

The socioeconomic profile had N = 424, 409 and 428 women for the Telephone, Physical and Passive follow-up categories respectively (refer to Table 1). All three categories showed the largest number of women in the age group of 24 to 35 years of age. Most of the women in all of the categories were of twenty years of age or less at the time of their marriage and the average age of husbands for majority was between 30 and 40 years range for all categories.

**Table 1 Tab1:** **Socio-demographic characteristics and participant’s profile by prospective client follow-up group***

Indicators	Telephone group	Physical group	Passive group
	N = 424	N = 409	N = 428
	%	%	%
**Age of women**			
15 – ≤ 24	10.4	7.8	8.2
>24 – ≤ 34	66.7	63.3	60.5
≥35	22.9	28.9	31.3
Average (S.D)	30.4 (4.7)	31.0 (4.9)	31.0 (5.2)
***P-value***	***0.06***		
**Age of women at time of marriage**			
≤20	62.0	63.8	62.6
>20 – ≤ 25	31.1	28.9	29.0
>25	6.8	7.3	8.4
Average (S.D)	20.3 (3.1)	20.3 (3.1)	20.6 (3.2)
***P-value***	***0.86***		
**Age of husband**			
≤30	23.1	17.4	20.6
>30 – < 40	46.7	47.2	41.6
≥40	30.2	35.5	37.9
***P-value***	***0.06***		
**Women education**			
No formal education	36.3	40.8	43.2
Can read/write	4.7	3.2	2.6
Primary	12.0	15.9	13.1
Middle	11.1	15.6	12.4
Secondary	25.7	17.4	19.4
Intermediate	6.1	4.9	5.1
Graduate/Post Graduate	4.0	2.2	4.2
***P-value***	***0.03****		
**Working women**			
Yes	9.7	8.6	6.8
Housewife	90.3	91.4	93.2
***P-value***	***0.30***		
**Husband education**			
No formal education	15.6	15.2	20.1
Can read/write	2.4	2.9	0.5
Primary	7.8	10.8	9.6
Middle	19.1	19.6	17.1
Secondary	42.2	42.8	43.9
Intermediate	8.5	6.4	4.4
Graduate/Post Graduate	4.5	2.4	4.4
***P-value***	***0.03****		
**Husband occupation**			
Unskilled manual	18.4	21.8	22.9
Skilled manual	21.9	21.5	21.7
Agriculture/Farming	11.3	16.6	17.3
Sales & services	17.0	14.9	13.8
Professional/Technical manager	17.5	12.7	13.3
Clerical/Office work	7.5	5.9	5.1
Household chores	2.6	1.5	1.9
Jobless	3.8	5.1	4.0
***P-value***	***0.20***		
**Family monthly income (PKR) (1 USD = 102 PKR)** ^**1**^			
≤5,000 (49 USD)	13.6	13.8	14.2
>5,000 – ≤10,000 (>49 USD – 98)	55.1	58.8	52.8
>10,000 – ≤15,000 (>98 USD – 147)	22.9	20.0	19.3
>15,000 (>147 USD)	8.4	7.4	13.6
Average (S.D)	10,282 (7654)	10,263 (9,149)	10,433 (5,166)
	100.8 USD (75)	100.6 (89.7)	102.3 (50.7)
Median	9,000	9,000	9,000
	88.2 USD	88.2 USD	88.2 USD
***P-value***	***0.12***		
**Type of client**			
Out of Pocket (referred by FHE)	5.0	9.8	8.4
Voucher	95.0	90.2	91.6
***P-value***	***0.03****		
**Type of Provider**			
*Suraj* SF (Rural)	67.0	68.7	69.6
Urban Provider (Urban)	33.0	31.3	30.4
***P-value***	***0.70***		
**FP method taken**			
IUD	78.5	85.3	85.0
Implant	21.5	14.7	15.0
***P-value***	***0.01****		

*Groups: Telephone group will receive a telephone call at the scheduled frequency; Physical group will receive household based follow-up, and Passive group category participants will not receive any scheduled intervention but can only seek assistance in case of any medical need.

^1^
http://www.forex.pk/open_market_rates.asp.

Majority of the women in all three categories had no formal education (observed as 36.3%, 40.8% and 43.2% for Telephone, Physical and Passive categories respectively).

Moreover the ‘type of client’ indicator showed that majority i.e. Telephone (95%), Physical (90.2%) and Passive (91.6%) obtained their FP services via vouchers. The percentage for IUCD uptake was 78.5%, 85.3% and 85% for Telephone, Physical and Passive categories respectively.

The majority of all three categories showed a favorable view of the husband with regards to using a contraceptive method (refer to Table 2).

**Table 2 Tab2:** **Family views regarding FP contraceptive by prospective client follow-up group**

Indicators	Telephone group	Physical group	Passive group
	N = 424	N = 409	N = 428
	%	%	%
**Husband’s view on couple using a contraceptive method**			
Favors	81.7	71.8	74.3
Dislikes	8.3	15.9	13.9
Don’t know/unsure	10.0	12.3	11.8
***P-value***	***<0.01***		
**Husband knows you have inserted IUCD/Implant**			
Yes	83.3	76.3	72.2
No	16.7	23.7	27.8
***P-value***	***<0.001***		
**Mother in law knows you have inserted IUCD/Implant**			
Yes	51.4	46.5	40.7
No	48.6	53.5	59.3
***P-value***	***<0.01***		

### Reproductive health and contraceptive history

Reproductive health and contraceptive history show that most of the women in each group had 3-4 pregnancies and also had similar number of living children as well (Refer to Table 3).

**Table 3 Tab3:** **Reproductive health and contraceptive history by prospective client follow-up group**

Indicators	Telephone group	Physical group	Passive group
	N = 424	N = 409	N = 428
	%	%	%
**Number of pregnancies**			
1 – 2	32.5	27.4	27.8
3 – 4	44.1	45.7	47.0
5 or more	23.3	26.9	25.2
Average (SD)	3.5 (1.8)	3.7 (1.8)	3.6 (1.8)
***P-value***	***0.43***		
**Number of living children**			
0 – 2	38.0	32.0	34.1
3 – 4	44.8	49.4	49.8
5 or more	17.2	18.6	16.1
Average (S.D)	3.1 (1.6)	3.3 (1.5)	3.2 (1.5)
***P-value***	***0.37***		
**Result of last pregnancy**			
Live birth	93.9	91.9	90.0
Still birth	3.8	5.1	5.4
Miscarriage/aborted	2.4	2.9	4.7
***P-value***	***0.25***		

The percentage of women who did not use any contraception in the past three months was 44% in each Telephone, Physical and Passive categories (Table 3). When questioned about ‘spacing’ with regards to the ‘desire to have more children’; many women expressed for a desired spacing period of 36 months before their next child.

### Information pertaining to IUCD/Implant services

Long acting effectiveness was the main reason for choosing IUCD/Implant among Telephone (61.3%), Physical (59.2%) and Passive (55.3%) categories. Similarly the decision to take up the service was made mostly by the women themselves in all three categories; while mutual decision by husband and wife was identified as second most common factor (refer to Table 4). It was noted that the majority of the participants (more than 75%) reported having no side effects during ICUD/implant insertion amongst all categories. Likewise, most of the women (more than 65%) didn’t get any painkillers to take home after the insertions.

**Table 4 Tab4:** **Reason and final decision making regarding insertion of IUCD/Implant by prospective client follow-up group**

Indicators	Telephone group	Physical group	Passive group
	N = 424	N = 409	N = 428
	%	%	%
**Reason for choosing IUCD/Implant**			
Suggested by FHE (Suraj)	7.9	8.3	9.6
Suggested by FHE (Urban)	7.4	8.8	8.2
Suggested by Suraj client	4.1	4.6	1.6
Long acting effectiveness	61.3	59.2	55.3
Freely available	7.2	7.6	7.7
Easily accessible	8.6	7.3	13.1
Others (fewer side effects, suggested by husband/LHW/Urban happy client)	3.5	4.1	4.4
***P-value***	***0.14***		
**Final decision made by**			
Myself	57.5	62.3	64.6
Husband	1.4	0.0	0.0
Both (husband & wife)	36.3	32.8	32.8
Mother in law	0.9	0.7	0.5
All together	3.8	1.9	1.9
***P-value***	***0.08***		
**Experienced side effects during IUCD/Implant insertion**			
Yes	21.9	24.4	21.5
No	78.1	75.6	78.5
***P-value***	***0.71***		
**Got the painkillers to take home**			
Yes	32.9	38.4	32.6
No	67.1	61.7	67.4
***P-value***	***0.35***		

### Counseling and quality of information provided

The majority of the clients reported that they received counseling on all family planning methods before they opted for IUD or Implant (refer to Table 5). As shown in Table 5, most of the women in Telephone (89%), Physical (91%) and Passive follow up (92%) categories got clear instructions in case they experience any side effects. Similarly, majority of the women among all categories got the method of their choice.

**Table 5 Tab5:** **Receive counseling on FP method before IUCD/Implant insertion by prospective client follow-up group**

Indicators	Telephone group	Physical group	Passive group
	N = 424	N = 409	N = 428
	%	%	%
**Contraceptive method (multiple responses)**			
None/Didn’t discuss any method	6.1	11.0	7.7
***P-Value***	***0.03***		
Condoms	80.7	75.1	74.8
***P-Value***	***0.07***		
Pills	84.0	78.7	80.6
***P-Value***	***0.15***		
Injections	85.8	80.0	84.3
***P-Value***	***0.06***		
IUCD	89.6	83.6	87.9
***P-Value***	***0.03***		
Implant	72.2	70.9	70.1
***P-Value***	***0.80***		
Female sterilization	17.0	23.0	19.4
***P-Value***	***0.09***		
Male sterilization	9.4	14.4	10.3
***P-Value***	***0.05***		
Withdrawal	4.5	5.9	5.6
***P-Value***	***0.64***		
Periodic abstinence	7.3	9.3	8.9
***P-Value***	***0.55***		
Emergency contraception	8.5	7.8	6.5
***P-Value***	***0.55***		

## Discussion

Based on the results of the study, we hope to identify a more convenient method of effective follow-up for managing side effects, health concerns and other potential reasons of method discontinuation and switching. The study information will also facilitate to develop a robust, effective and efficient mechanism for client follow-up in Suraj Social Franchise model for FHEs to promote the continuation rates of LARC methods. The follow-up results and lessons learnt will be widely shared with stakeholders (both amongst government and private sector) for their replication in health system. We will also use the follow-up findings to contribute to the knowledge base through publications in peer reviewed journals, working paper series and relevant international/regional conferences.

Depending on the results it is anticipated that we will have relatively efficient, easy and less tiring (less mobility) approach to ensure post-method uptake follow-up. This will also provide supportive environment in managing post-insertion follow-up for LARC users in the rural areas in order to reduce higher method discontinuation and switching. We hope study findings will help large cadre of LHWs and other outreach workers to effectively follow-up clients and eventually leading to reduction in contraceptive discontinuation in the country.

